## Abstract

**Background:**

Chronic pain affects approximately 8 million Canadians (~20%), impacting their physical and mental health while burdening the health care system with costs of upwards of US $60 billion a year. Indeed, patients are often trialed on numerous medications over several years without reductions to their symptoms. Therefore, there is an urgent need to identify new therapies for chronic pain to improve patients’ quality of life, increase the availability of treatment options, and reduce the burden on the health care system.

**Objective:**

The primary objective of this study is to examine the feasibility of a parallel 3-arm pilot randomized controlled trial whereby patients are randomized to either intravenous ketamine alone, cognitive behavioral therapy (CBT) and mindfulness meditation (MM) training (CBT/MM), or the combination of intravenous ketamine and CBT/MM. The secondary outcome is to assess the durability and efficacy of combination intravenous ketamine and CBT/MM for treatment of chronic pain as compared to CBT/MM or intravenous ketamine alone (assessed at week 20 of the study).

**Methods:**

This is a single-center, 16-week, 3-arm pilot study that will take place at the Chronic Pain Clinic at St. Michael’s Hospital, Toronto, Ontario, which receives 1000 referrals per year. Patients will be enrolled in the study for a total of 20 weeks. Participants who are allocated CBT/MM therapy will receive remote weekly psychotherapy from week 1 to week 16, inclusive of health coaching administered through the NexJ Health Inc (NexJ Health) platform. Patients who are allocated ketamine-infusion therapy will receive monthly ketamine infusion treatments on weeks 2, 7, and 12. Patients who are allocated ketamine+CBT/MM will receive weekly psychotherapy from weeks 1 to 16, inclusive, as well as ketamine infusion treatments on weeks 2, 7, and 12. We will be assessing recruitment rates, consent rates, withdrawal rates, adherence, missing data, and adverse events as pilot outcome measures. Secondary clinical outcomes include changes relative to baseline in pain intensity and pain interference.

**Results:**

As of November 1, 2023, the recruitment process has not been initiated. Given the recruitment, consent, and intervention target of 30 participants for this feasibility study, with each patient undergoing monitoring and treatments for a course of 20 weeks, we expect to complete the study by December 2025.

**Conclusions:**

This study assesses the feasibility of conducting a 3-arm randomized controlled trial to examine the effects of ketamine administration with the concurrent use of CBT/MM in a population with chronic neuropathic pain. The results of this pilot randomized controlled trial will inform the development of a larger-scale randomized controlled trial. Future studies will be aimed at including a sufficiently powered sample that will inform decisions about optimal treatment calibration and treatment effect duration.

**Trial Registration:**

ClinicalTrials.gov NCT05639322; https://classic.clinicaltrials.gov/ct2/show/NCT05639322

**International Registered Report Identifier (IRRID):**

PRR1-10.2196/54406

## Introduction

Chronic pain affects approximately 8 million Canadians (~20%) and profoundly impacts their physical and mental health. The broad ranging consequences of this disease are evidenced by estimated health care system costs upwards of US $60 billion a year [1]. In the United States, chronic pain also affects 1 in 5 people, and the annual cost is estimated as greater than US $0.5 trillion [2]. Indeed, chronic pain is associated with poor quality of life, psychiatric symptoms, and mobility restrictions. It has significant physical, functional, social, and economic impacts at the individual and system levels. Current pain therapies aim to decrease pain to manageable levels. In most cases however, chronic pain cannot be completely eliminated. Patients are often trialed on numerous medications without adequate relief, and therapies are often limited by their lack of durability and adverse effects. There is an urgent need to identify new therapies for chronic pain to improve patients’ quality of life and the availability of treatment options, while reducing health care system burdens.

Ketamine is an N-methyl-D-aspartate receptor antagonist which results in pain reduction. It is also associated with reductions in opioid-induced hyperalgesia and opioid consumption [3]. At high doses, it is an agonist at the mu receptor, the D2-R, and L-Type voltage-gated calcium channel. Current evidence supports intermittent ketamine therapy for neuropathic pain. Double-blind randomized controlled trials (RCTs) investigating the use of ketamine for neuropathic pain have demonstrated clinically significant reductions (25% to 43%) in chronic pain versus control conditions [3]. However, ketamine appears to have limited durability as studies have shown short term reductions in neuropathic pain secondary to spinal cord injury and fibromyalgia but no long-term benefits [4,5]. Although timelines and follow-ups vary significantly, the lack of durability is consistent across all ketamine infusion regimens studied [6]. Indeed, a systematic review by Cohen et al [3] indicated a lack of evidence for durable benefits, affirming the need for adjunctive therapies that improve durability and improve outcomes.

Internet-delivered cognitive behavioral therapy (CBT) for chronic pain, depression, and anxiety is associated with significant reductions in pain disability, symptoms of depression, and pain catastrophizing at 1 year follow-up [7]. Nonetheless, an integrative review [8] concluded CBT research must further address longer-term efficacy (>12 months). This same review highlighted the significant variations in the duration and total dose hours of CBT interventions and delivery methods (remote, group, or individual). Despite variations, existing studies and emergent guidelines support the synergistic effects of pharmacological therapies strategically combined with CBT-based strategies [7].

The primary objective of this trial is to study the effects of concurrent ketamine and CBT for chronic neuropathic pain relief. Biological and neurocognitive factors suggest that concurrent pharmacotherapy and psychotherapy can result in more durable and effective analgesic responses than either intervention alone. Ketamine administration induces physiological changes during and after delivery that result in powerful experiential responses with important psychological and emotional impacts [9]. The physiological changes associated with ketamine therapy are likely to influence important habitual thinking and behavior patterns. Studies suggest that ketamine alters functional brain connectivity, even to the point of disrupting spatiotemporal patterns of neural activity and increasing functional communications between brain regions typically isolated [9].

Despite the biologic plausibility of ketamine-assisted psychotherapy being an effective cotreatment for chronic neuropathic pain, there is a lack of rigorous evidence supporting its use. Our group conducted a systematic review to examine existing evidence on concurrent ketamine dosing and psychotherapy [10]. This knowledge synthesis showed substantial methodologic variations across 17 studies. The most common indications studied included posttraumatic stress disorder (6 studies), major depressive disorder (6 studies), substance use disorder (6 studies), and obsessive compulsive disorder (2 studies). Only 2 publications (a case report and a case series) examined continuous multiday ketamine infusions with concurrent psychotherapy in individuals with chronic pain. Ocker et al [11] described a 5-day continuous ketamine infusion regimen combined with CBT to successfully taper opioids in a patient with complex regional pain syndrome who was taking 330 mg of daily morphine equivalents. They attribute the sustained results to an observed synergism between ketamine and the outpatient CBT protocol. Keizer et al [12] described a case series of 11 patients who received ketamine-enhanced psychotherapy for comorbid neuropathic pain and posttraumatic stress disorder. A 96-hour ketamine infusion was delivered with daily bedside psychotherapy. Although it resulted in a moderate but clinically meaningful reduction in pain symptoms, the brief follow up of 5 days precluded in-depth examination of the potential synergism.

This systematic review also revealed no evidence that a single protocol or therapy strategy was decidedly more beneficial than any other. To date, no RCT has combined ketamine and psychotherapeutic intervention for patients with chronic pain. The results of this review highlight the poor methodological quality of existing studies and need for higher quality evidence on the potential impact of combined interventions. By means of this pilot study, our intention is to determine whether a customized CBT along with mindfulness and meditation (MM; ie, CBT/MM) psychotherapy regimen can be effectively and safely integrated with a ketamine-induced state in a chronic neuropathic pain sample.

The Psychotherapy for Ketamine’s Enhanced Durability in Chronic Neuropathic Pain study has received partial funding from the Canadian Pain Society in partnership with the Pfizer Early Career Investigator Award as well as the St. Michael’s Hospital Association Innovation Fund.

## Methods

### Aim

The primary objective of this study is to enroll 30 participants with chronic neuropathic pain and assess the feasibility of conducting a 3-arm parallel group pilot RCT. The secondary aim of the study is to examine whether the combined effects of ketamine and CBT/MM (as delivered through the NexJ Health Inc platform by trained navigator-coaches) can reduce pain intensity and pain interference by week 20 of the study (ie, limited efficacy at week 20).

### Recruitment and Randomization

Recruitment will occur at the Chronic Pain Clinic at St. Michael’s Hospital, Toronto, Ontario. The clinic receives approximately 1000 referrals per year. An estimated 3% of these referrals would be eligible for inclusion in this trial.

A staff member who does not belong to the study team will be provided with the instructions to use a remote random number generator, the “Sealed Envelope” website to generate an allocation sequence at random. The allocation list will be sent to the Research Pharmacy staff at St. Michael’s Hospital directly, without the knowledge of the study team, to maintain the blindness. After participant enrollment, the pharmacy staff will randomize the patient and inform a delegated research team member as to the allocated intervention arm. The delegated unblinded research team member will then notify the patient which arm they have been randomized to and will coordinate with the anesthesiologists and psychologists, who will be unblinded, to schedule in-person study visits on weeks 2, 7, and 12 according to the randomized treatment arm. For patients randomized to Arm 1 or 3, the Research Pharmacy staff will prepare ketamine-hydrochloride for weeks 2, 7, and 12. The outcome assessors are the only research staff to remain blinded to patient treatment (currently, we only have 1 delegated outcome assessor).

Participants will be randomized to receive either (1) ketamine-hydrochloride infusions alone, (2) CBT/MM alone, or (3) a combination ketamine-hydrochloride infusion and CBT/MM.

Participants will be eligible for this study as per the inclusion and exclusion criteria listed (Textbox 1).

Inclusion and exclusion criteria regarding participant eligibility for PYSKED-NP.

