#### Hypothesis

In line with the primary aim of this study, this pilot study will prove to be feasible for a large-scale clinical trial. We expect that we will be able to successfully meet our recruitment target (30 participants) within the 1-year time frame of the study and expect this study withdrawal rate to be less than 10% (3/30 patients). Feasibility of this study will be determined by the following set variables and cutoff percentages; recruitment success with the specific aim to recruit all necessary patients within the first year of the trial period, adequate consent rate (30/100, >30% of eligible patients consent to participate in the study), intervention adherence as define by the percentage of patients who complete all medication and psychotherapy visits (27/30, >90%), percentage of patients who withdraw from the study (ie, due to side effects; 6/30, <20%), percentage of patients with incomplete pain intensity and pain interference data at 1 month, (eg, withdrawal due to side effects, loss to follow up, or missing data; 3/30, <10%), and rate of adverse outcomes. We do not foresee any issues arising with the protocol of the study or the delivery of each arm.

While not powered to examine these effects, we hypothesize that patients allocated to the combination ketamine and CBT/MM arm of this study will have the greatest reduction in pain intensity and pain interference.

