### Outcome Measures

#### Primary Outcome

The primary outcome of this pilot trial is to determine the feasibility of a large-scale multicenter trial. Feasibility outcomes will include the following variables, with all thresholds listed in parentheses:

Recruitment success (with the specific aim of recruiting all necessary patients within the first year of the trial period).Adequate consent rate (>30% of eligible patients consent to participate in the study).Percentage of patients who complete all medication and psychotherapy visits (ie, intervention adherence; >90%).Percentage of patients who withdraw from the study (eg, due to side effects or other reasons; <20%).Percentage of patients with incomplete pain intensity and pain interference data at 1 month and stated or ascribed reason (eg, withdrawal due to side effects, loss of follow-up, or missing data; <10%).Rate of adverse outcomes (ie, 0 serious adverse events).

Based on the result for each primary feasibility outcome, we will determine whether the definitive study is feasible as proposed (ie, all feasibility targets are met), feasible with protocol modifications (modifications specified), or not feasible because feasibility targets could not be met even with protocol modifications. These cutoffs, identified in the parentheses above, will help determine whether protocol changes are required before proceeding with a definitive trial.

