## Results

### Prestudy Screening

Eligible participants will be screened at the Chronic Pain Clinic at St. Michael’s Hospital. Participants diagnosed with chronic neuropathic pain that meet the criteria from the ID pain questionnaire will be approached and asked to consider study participation.

After participants have provided informed consent, they will be asked about their medical comorbidities, psychiatric history as based on the Mini International Neuropsychiatric Interview, history of ketamine hypersensitivity, and concomitant medications to confirm eligibility. If a participant is eligible to participate in the study, the participant will be enrolled in the study, and the study coordinator will book an appointment for the participant’s study intervention.

At this current point, November 1, 2023, the study has not started enrolling and consenting patients.

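### With 3% of about 1000 referrals eligible, recruiting 30 participants in one year needs essentially 100% consent, yet a rate just above 30% is called adequate

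*Protocol article*

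**What the plan says.** All the figures come from the protocol article.

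- **Patient supply** (Recruitment and Randomization): "The clinic receives approximately 1000 referrals per year. An estimated 3% of these referrals would be eligible for inclusion in this trial". One clinic is named, and no other source of patients is quantified.
- **Recruitment target** (Hypothesis): the authors expect that "we will be able to successfully meet our recruitment target (30 participants) within the 1-year time frame of the study". Primary Outcome makes this the first feasibility criterion, "with the specific aim of recruiting all necessary patients within the first year of the trial period".
- **Consent target** (Hypothesis): "adequate consent rate (30/100, >30% of eligible patients consent to participate in the study". Primary Outcome repeats the >30% threshold without the fraction 30/100.
- **Completion date** (abstract, Results): "we expect to complete the study by December 2025".
- **Use of the criteria** (Primary Outcome and Outcome Analysis): the definitive trial is feasible as proposed if all targets are met. The other two verdicts are feasible with protocol modifications and not feasible.

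**The concern.** Feasibility is the primary outcome of this pilot, and recruitment and consent are the first two of its criteria. They are links in one chain: referrals, times the fraction eligible, times the fraction consenting, gives enrolment. The supply figure and the recruitment target leave no room for anyone to decline, while the consent criterion is content with nearly 70% declining.

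If the figures do not fit together, the consent threshold gives no assurance about recruitment. The pilot could record adequate consent alongside a large recruitment shortfall, and the reader could not tell whether the shortfall reflected patients' reluctance or a planning figure that was wrong from the start. The pilot is meant to inform a larger multicentre trial, so that distinction matters.

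**Working it through.** **Inputs.** Referrals R = 1000 a year and eligible fraction e = 3% (Recruitment and Randomization); target N = 30 in one year (Hypothesis, Primary Outcome); consent threshold c = 30%, also written 30/100 (Hypothesis).

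**Step 1: eligible patients a year.** R × e = 1000 × 0.03 = 30.

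**Step 2: consent needed for 30 in one year.** N / (R × e) = 30/30 = 100%. If 3% is a rounded figure, 2.5% gives 25 eligible and 30/25 = 120%, which is impossible. A fraction of 3.5% gives 35 eligible and 30/35 = 86%. Rounding does not close the gap.

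**Step 3: enrolment at the threshold.** 30 × 0.30 = 9 a year. Time to 30 is 30/9 = 3.3 years. The one-year shortfall is (30 − 9)/30 = 70%.

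**Step 4: supply implied by 30/100.** The other counts in the same sentence (27/30, 6/30, 3/30) use the actual trial size, so 30/100 reads naturally as 30 enrolled from 100 eligible. In one year that needs 100/1000 = 10% of referrals eligible, against the stated 3%.

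**Step 5: enrolment and chance at other consent rates.** The probability of at least 30 enrolled in one year assumes that each of 1000 referrals enrols independently with probability 0.03 × consent. The 70% and 90% rows use the Poisson approximation with the expected number as mean.

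| Consent | Expected in 1 year | Years to 30 | P(at least 30 in 1 year) |
|---|---|---|---|
| 30% | 9 | 3.3 | about 2 in 100 million |
| 50% | 15 | 2.0 | 0.0004 |
| 70% | 21 | 1.4 | 0.04 |
| 80% | 24 | 1.25 | 0.13 |
| 90% | 27 | 1.1 | 0.31 |
| 100% | 30 | 1.0 | 0.52 to 0.53 |

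**Step 6: a reading under which everything fits.** If 3% was meant as the share of referrals enrolled, then 10% eligible × 30% consent = 3%, and 1000 × 0.03 = 30 a year. This reproduces every figure, but the text says eligible, not enrolled.

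**Step 7: the completion date.** The article gives no recruitment start date. Assume it was as early as possible, November 2023. To December 2025 is then about 26 months, and taking off 20 weeks of follow-up (about 4.6 months) leaves about 21.4 months. Eligible patients: 30 × 21.4/12 ≈ 53. Consent needed for 30: 30/53.5 ≈ 56%. At 30% consent about 16 would be enrolled.

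**The case against.** **A minimum is not a forecast.** The >30% is a floor, and the article nowhere predicts that consent will sit there. If 30 of 30 eligible patients consented, both criteria would be met. This stands, so the criteria are not contradictory in logic. The figures of 9 a year and 3.3 years describe a trial that just passes the consent criterion, not an expected outcome.

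**The verdict is not fixed in advance.** A reader might infer that the pilot is bound to fail. The documents do not support that: both criteria can be met together, and the plan allows a verdict of feasible with modifications, so missing the one-year window would not by itself mean not feasible.

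**30/100 may only be a percentage written as a fraction.** This is possible. The consent criterion could not use the enrolled 30 as its denominator, so the pattern of the other counts is suggestive rather than proof. The 100 eligible patients are therefore an inference. Steps 1 to 3 do not depend on it.

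**Other patients may be available.** The article does not restrict screening to that year's new referrals, so 30 a year is not shown to be a hard ceiling. But no existing pool or second site is quantified, and the referral count is the only supply figure offered.

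**The completion date.** It might seem to conflict as well. It does not: on the assumption in step 7, about 56% consent would suffice. Nor does it resolve the one-year criterion.

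**The consent denominator.** Prestudy Screening says "After participants have provided informed consent, they will be asked about their medical comorbidities" and other eligibility items, so one might infer that consent among eligible patients cannot be calculated. That goes too far. Patients are approached after a diagnosis and the ID pain criteria, which gives a workable denominator, and the exact definition is something a condensed article can leave to the full protocol.

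**Conclusion.** The concern holds as an inconsistency between planning figures. On the article's own inputs, about 30 patients a year are eligible, so the one-year target needs essentially 100% consent (86% if the true fraction were 3.5%). Even at 100% consent, the chance of reaching 30 is only about 52%. A consent rate just above the threshold would yield about 9 participants in the year and miss the target by about 70%. If 30/100 is a planned count, it also implies an eligible fraction of 10% rather than 3%.

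This rests on two assumptions: that annual referrals are the patient source, as the article presents them, and that 3% means eligible, as written. The probabilities also assume independent referrals. The likeliest explanation may be a wording slip, with 3% meaning the share enrolled, but the text would still need correcting. The finding does not show that the feasibility verdict is predetermined or that the consent rate is incalculable.

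**What to change.** Check the eligible fraction against the clinic's referral records, then restate whichever figure is wrong so that referrals × eligible fraction × consent rate equals the target enrolment rate:

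- **Eligible fraction:** if 3% was meant as the share enrolled, state about 10% eligible (1000 × 0.10 × 0.30 = 30 a year).
- **Consent threshold:** if 3% eligible and one year both stand, the threshold must be close to 100% to support the target.
- **Recruitment window:** if 3% and 30% both stand, about 3.3 years is needed, and the completion date must move with it. At 50% consent the window would be 2.0 years.

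If other patients at the clinic are to be approached, give their number. As an optional clarification, state the consent rate as consented over approached after the pre-consent screen.

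The cost is a look at existing records and a change of wording, with no added patients. The drawback is that the stated timeline or threshold may become less favourable. The article reports that recruitment had not begun on November 1, 2023; a correction made before enrolment starts would not be influenced by trial data.

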**Inclusion criteria**
Aged 18 years or older.Diagnosis of chronic neuropathic pain as determined by a pain specialist with moderate to severe neuropathic pain as per ID pain questionnaire, with mean pain scores >3 on an 11-point (0-10) Numeric Rating Scale, in the 7 days preceding inclusion.For participants of childbearing potential, use of highly effective or double-barrier methods of contraception. Abstinence is acceptable if it is the preferred and usual lifestyle of the participant.Capacity to provide informed consent
